#### Primary hypothesis (H1)

Foster carers who participate in the COS-P program will demonstrate a significant improvement in caregiving sensitivity at the 3-month follow-up assessment, as measured by the Caregiving Composite Questionnaire (CCQ). Specifically, we hypothesize that, compared to the waitlist control group, foster carers completing COS-P will, at the 3-month follow-up assessment, show.

(H1a) a greater increase in parental mentalizing,

(H1b) a greater increase in parenting self-efficacy, and.

(H1c) more positive perceptions of the child.

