#### To explore potential moderators of intervention outcomes

This will include examining the influence of foster carer burnout, emotional support provided by Child Protection Services, and fidelity of program implementation.

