### Measures

#### Three-time measurement

Following an initial phase (T0), data collection will occur at three time points (see Table 3):

**T1 (Baseline)** Questionnaires, interviews, and interaction assessments will be administered in the week prior to the first COS-P session.

**T2 (3-month f/u)** Questionnaires, interviews, and interaction assessments will be administered three months after the final COS-P session.

**T3 (Qualitative Data Collection at 4-month f/u)** Focus groups will be conducted four months after the completion of the intervention (see Table 4 for an overview of assessments).

**Table 3 Tab3:** SAFE FAMILIES study data collection schedule

	(T0) Enrollment and allocation	(T1) Baseline	COS-*P* group (intervention arm only)	(T2) 3-month f/u	(T3) 4-month f/u
Foster Parent Consent	X				
Biological Parent Consent (video recording)	X				
Sociodemographic and Professional Questionnaire	X				
*Quantitative assessments*					
CCQ		X		X	
PSI		X		X	
PBA		X		X	
SAQ		X		X	
MSPE		X		X	
MIM-DEIS		X		X	
PDI-R		X		X	
COS-P Fidelity Log			X		
*Qualitative assessments*					
Self-Confrontation Interviews		X		X	
Focus-groups					X

**Table 4 Tab4:** Overview of qualitative and quantitative assessments

	Control Group (Gc) + Intervention Group (Gi) *N* = 70	Subgroups of Gi
	Quantitative assessments	Qualitative assessments
**Primary Outcome** Assess foster parent caregiving sensitivity and reflective functioning	CCQ	PDI-R (*N* = 20) Self-confrontation Interviews (*N* = 6)
**Secondary Outcome** Assess the relationship between the foster parent and the child		
	PSI	SMRC (*N* = 20), MIM-DEIS (*N* = 20) Focus Groups

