### Statistical analyses

***Sample size and analysis.*** Sample size calculation was based on an effect size of *d* = 0.38, drawn from a meta-analysis examining the impact of attachment-based interventions on parental sensitivity [49]. An a priori power analysis using G*Power software [50] indicated that 58 participants are needed to achieve 80% power with a significance level of *p* <.05. To account for potential attrition (20%), we aim to recruit 35 participants for each group (intervention and waitlist control receiving TAU).

The data will be analyzed using both quantitative and qualitative methods. Statistical analyses will be conducted using R software. All tests will be two-tailed with a significance level set at *p* <.05.

***Quantitative analyses.*** Descriptive statistics will be used to characterize the sample at baseline (T1) and at each assessment point (T2, T3). This will include frequencies and percentages for categorical variables (e.g., gender) and means and standard deviations for continuous variables (e.g., age, duration of placement). To test the primary hypothesis (H1), a two-way mixed ANOVA will be conducted with Group (Intervention vs. Control) as the between-subjects factor and Time (T1, T2) as the within-subjects factor. The dependent variable will be the CCQ score. To test the secondary hypothesis (H2), a two-way mixed ANOVA will be conducted with Group (Intervention vs. Control) as the between-subjects factor and Time (T1, T2) as the within-subjects factor. The dependent variable will be the PSI score. To explore the potential moderating effects of parental burnout (PBA), perceived emotional support from placement services (SAQ) and fidelity of program implementation, hierarchical multiple linear regressions will be performed. The CCQ and PSI scores at T2 will be the dependent variables, with group allocation (Intervention vs. Control) as the primary predictor. The potential moderators (PBA, SAQ, and fidelity of implementation) will be entered in the model after the main effect of group allocation.

Complementary Analyses for a Subgroup of Foster Carers: A subgroup of 20 foster carers will participate in additional assessments using the Parent Development Interview - Revised (PDI-R) and the Marschak Interaction Method (MIM) coded with the Dyadic Emotional Interaction Style (D-EIS). These assessments will be conducted at T1 (baseline) and T2 (3-month follow-up).

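### The exploratory moderator regressions omit the T1 score of their own outcome, so a burnout or support coefficient would carry the carer's starting level

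*Protocol article*

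**What the plan says.** The Statistical analyses section of the protocol article gives the purpose of the regressions as "To explore the potential moderating effects of parental burnout (PBA), perceived emotional support from placement services (SAQ) and fidelity of program implementation". It then fixes the outcome and first predictor: "The CCQ and PSI scores at T2 will be the dependent variables, with group allocation (Intervention vs. Control) as the primary predictor". The later step is: "The potential moderators (PBA, SAQ, and fidelity of implementation) will be entered in the model after the main effect of group allocation". No T1 CCQ or PSI score, change score or group-by-moderator product is named, and the time point of PBA and SAQ is not given.

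H1 and H2 are tested differently. For H1 the model is a mixed ANOVA with "Group (Intervention vs. Control) as the between-subjects factor and Time (T1, T2) as the within-subjects factor. The dependent variable will be the CCQ score", and H2 uses the same design for the PSI. The group-by-time term of that design is the between-arm difference in T1-to-T2 change.

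The T1 scores exist. Under Three-time measurement, T1 is described as: "Questionnaires, interviews, and interaction assessments will be administered in the week prior to the first COS-P session". Table 3 marks CCQ, PSI, PBA and SAQ at both T1 and T2, and places the fidelity log in the column for the intervention arm only.

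**The concern.** A carer who is burned out at the start is likely also to score worse on the CCQ and PSI at the start, and to remain somewhat worse at T2. The PBA's exhaustion and emotional-distancing dimensions lie close to the CCQ's helplessness and hostility subscales and to the parent-child dysfunctional interaction subscale of the PSI. With no T1 score in the model, the PBA coefficient takes up that persistence. The same applies to the SAQ in so far as it correlates with the T1 outcome.

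The second step could then add significant explained variance for burnout or support when neither is related to T2 beyond the starting score. The Discussion expects the findings to inform interventions that address burnout and support networks, so these coefficients are likely to be used.

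Two smaller consequences follow. The model leaves in residual variance that T1 would remove. Its group estimate is also a different contrast from the one in the ANOVA for the same outcome.

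**Working it through.** **Inputs from the protocol article.** d = 0.38; 58 carers needed; 35 per arm recruited; 20% attrition; two-sided 5% tests; simple randomization. Carers analysed: 70 × 0.8 = 56, or 28 per arm.

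**Assumed, because the documents do not give them.** T1–T2 correlation rho of 0.5 to 0.7; correlation r between PBA and T1 CCQ of -0.3 to -0.5. Scores are in SD units.

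**The plan's own figure.** The stated 58 is reproduced by the repeated-measures within-between interaction with f = d/2 = 0.19, two groups, two times and rho = 0.5: lambda = 0.19² × 58 × 2 / 0.5 = 8.38, power 0.81. Fifty-six carers give 0.7975. So rho = 0.5 is compatible with the sample size, though the article does not state it.

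**1. Moderator main effect.** Let T2 = rho·T1 + 0.38·group + error, and let PBA correlate r with T1 and have no effect on T2 once T1 is known. Regressing T2 on group and PBA alone gives a PBA coefficient of about rho × r, with standard error about √[(1 − (rho·r)²)/53].

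- rho 0.5, r -0.3: coefficient -0.15; SE √(0.9775/53) = 0.136; ratio 1.10; chance of significance about Φ(1.10 − 1.96) ≈ 20%.
- rho 0.7, r -0.5: coefficient -0.35; SE √(0.8775/53) = 0.129; ratio 2.72; chance about Φ(2.72 − 1.96) ≈ 78%.

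Simulation (4,000 trials per setting, 28 per arm) agrees:

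| rho | r | PBA significant, no T1 | PBA significant, T1 in model |
|---|---|---|---|
| 0.5 | -0.3 | 18–19% | 5% |
| 0.5 | -0.5 | 45–46% | 5% |
| 0.7 | -0.3 | 35% | 5% |
| 0.7 | -0.5 | 76–77% | 5% |

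**2. Group-by-moderator term, if one is added.** With no true interaction, it is rejected in about 5% of trials with or without T1, so omitting T1 does not bias it. Power does change:

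| Assumed interaction (SD per SD) | No T1 | With T1, rho 0.5 | With T1, rho 0.7 |
|---|---|---|---|
| 0.3 | about 18–22% | about 22–24% | about 30–33% |
| 0.6 | about 56–62% | about 66–67% | about 82–83% |

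**3. Group estimate at step 1.** Write D1 and D2 for the between-arm differences in mean T1 and T2 score. The T2-only estimate is D2 and the ANOVA change effect is D2 − D1. They differ by exactly D1, the chance T1 imbalance, with SD √(2/28) = 0.267. That is 0.267/0.38 = 70% of the planned effect. Both have expectation 0.38. With T1 in the model the estimate is D2 − b·D1, where b is about rho, so the gap is about (1 − rho)·D1. Its SD is 0.5 × 0.267 = 0.13 at rho 0.5 and 0.3 × 0.267 = 0.08 at rho 0.7 (simulated: about 0.14 and 0.08–0.09).

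**4. Precision of the group estimate.** The SE falls from 0.267 to 0.267 × √(1 − 0.25) = 0.231 at rho 0.5, or 0.267 × √(1 − 0.49) = 0.191 at rho 0.7. Simulated power for 0.38 rises from about 29% to about 35%, or to about 48–50%.

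**The case against.** **The PBA main effect is not a moderation test.** Once a product term is present, moderation is read from that term, and omitting T1 does not bias it. This stands. The 18–77% applies to the model as written, where no product term is named; with one added, what remains for the moderation question is lost precision.

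**A significant PBA coefficient is not strictly a false positive.** PBA is then truly associated with the T2 level. This also stands: the error arises when the coefficient is read as an influence on the response to COS-P. The stated aim invites that reading: "This will include examining the influence of foster carer burnout, emotional support provided by Child Protection Services, and fidelity of program implementation", under a heading about moderators of intervention outcomes.

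**H1 is not purely about change.** H1a speaks of "a greater increase in parental mentalizing", but H1c is worded as a level, and the moderators are objectives separate from H1 and H2. So a mismatch with H1's wording is weak support, and the point does not rest on it.

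**The group estimates.** A reader might infer that the trial will report two conflicting COS-P effects, one of them biased. The documents do not support that. H1 and H2 are assigned to the ANOVA, both contrasts have the same expectation under randomization, and the exact identity holds only before moderators enter. T1 adjustment narrows the gap without closing it.

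**Size.** An interaction of 0.6 exceeds the planned main effect of 0.38; at 0.3 power is low either way. For the SAQ there is no basis for any particular correlation with the CCQ, so no size is claimed.

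**The unseen analysis plan.** It might add the covariate, and the analysis is exploratory. But the article states outcome, first predictor and entry order; the comment is on that stated model.

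**Conclusion.** The point holds as a limited one about an exploratory analysis. As written, a PBA or SAQ coefficient would mix any relation to T2 with the carer's starting score. For PBA, under the assumed correlations, a coefficient with nothing behind it beyond T1 reaches significance in about 18–77% of trials instead of about 5%. The size depends on rho and r. The direction of the carry-over follows from their signs, and it vanishes only if either is zero.

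It would go too far to infer that a proper group-by-moderator test would be biased or that the primary or secondary conclusions are at risk: the first loses only power, and the H1 and H2 tests are separate models that use both time points. The amendment is still worth making, because the covariate is already collected and 56 analysed carers leave little precision to spare.

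**What to change.** In the hierarchical regressions, enter the T1 score of the same outcome with group allocation in step 1 (T1 CCQ for T2 CCQ, T1 PSI for T2 PSI), before any moderator. State that PBA and SAQ enter as their T1 values, since T2 values are taken after COS-P and may be altered by it. State that PBA and SAQ main effects will not be interpreted as moderation.

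This takes a sentence or two and no new data. It costs one degree of freedom, and carers without a T1 score drop out of these regressions, as they already do from the mixed ANOVA.

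This change does not deal with fidelity. Because the log exists in the intervention arm only, fidelity cannot moderate the group contrast in this model and needs separate treatment.

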**Fidelity of implementation** (**COS-P Fidelity Log).** This log consists of 12 Likert-scale items per session (96 items in total) and reflective questions, allowing facilitators to self-assess the fidelity and quality of program implementation with their group. For the purposes of this study, only the 96 Likert-scale items will be used for data analysis.

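### The exploratory moderation regressions, as described, contain no group-by-moderator term, and they include fidelity, which is recorded only in the COS-P arm, so they do not test moderation

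*Protocol article*

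**What the plan says.** Under its objectives, the protocol article lists the exploration of moderators of the intervention's outcomes, by "examining the influence of foster carer burnout, emotional support provided by Child Protection Services, and fidelity of program implementation".

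The quantitative part of Statistical analyses turns this into a model. The purpose is given as "To explore the potential moderating effects of parental burnout (PBA), perceived emotional support from placement services (SAQ) and fidelity of program implementation", and for this "hierarchical multiple linear regressions will be performed". The dependent variables are the CCQ and PSI scores at T2, "with group allocation (Intervention vs. Control) as the primary predictor". The next step is: "The potential moderators (PBA, SAQ, and fidelity of implementation) will be entered in the model after the main effect of group allocation". The description ends there. No interaction or product term appears in this section or elsewhere in the article.

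Three other places bear on the point:

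- **Fidelity.** The description of the COS-P Fidelity Log says that it consists of 12 items for each of the eight sessions, "allowing facilitators to self-assess the fidelity and quality of program implementation with their group". The rating therefore describes a group's sessions, not an individual carer. Table 3 marks the log only in the column headed "intervention arm only".
- **Control condition.** Controls receive usual support only and join COS-P later, so they have no sessions to rate during the comparison.
- **Timing of PBA and SAQ.** Table 3 schedules both at T1 and T2. The regression paragraph does not say which value is used.

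**The concern.** A moderator is a variable across whose levels the treatment effect differs. A model with group and moderator as separate additive terms fits the same treatment effect at every level of the moderator, so none of its coefficients measures that difference. What the second step does test is whether burnout or support predicts the outcome on average across both arms. Carers with more burnout may well score worse whichever arm they are in. That would give a significant second step which could then be reported as moderation.

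Fidelity raises a separate problem. It has no value in the control arm, so no comparison between arms can show how the COS-P effect varies with it.

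The stake is a declared exploratory objective. The Discussion says that the findings could inform tailored interventions aimed at burnout and support networks, and a prognostic association read as moderation would misdirect that use.

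**Working it through.** The plan gives no figure for the moderation analysis, so there is none to reproduce. The check has two parts.

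**1. PBA and SAQ: what the planned coefficient tests**

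Inputs from the article: 35 carers per arm and 20% attrition, so 35 × 0.80 = 28 per arm and 56 in total; d = 0.38 as the group effect; two-sided 5% level. Inputs assumed: a standard normal moderator, and the slopes listed below.

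Model as described: Y = b0 + b1·G + b2·M. Model that tests moderation: Y = b0 + b1·G + b2·M + b3·(G × M). Moderation is b3, the difference in slope between the arms.

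Share of simulated trials with p < .05:

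| Assumed truth | N | Planned term (b2, no product) | Product term (b3) |
|---|---|---|---|
| Prognostic only, r = 0.4, no moderation | 56 | 88% | 5% |
| Prognostic only, r = 0.3, no moderation | 56 | 60% | 5% |
| Prognostic only, slope 0.5, no moderation | 58 | 94% | 4.9% |
| Crossing slopes, -0.4 and +0.4 | 56 | 7% | 86% |
| Slope 0 in controls, 0.4 under COS-P | 56 | about 31% | about 31% |

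Repeat runs gave the same picture within about two percentage points. In the first three rows there is no moderation, and the planned term is nonetheless significant in most trials. In the fourth row moderation is strong and the planned term rarely detects it. In the fifth row the two terms reject equally often, but b2 does so because the average slope is not zero. It cannot tell that case from a purely prognostic variable.

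Power of the product term: with unit residual SD and n per arm, the standard error of the slope difference is about √(2/n). For n = 29 this is √(2/29) = 0.263, and a slope difference of 0.38 gives 0.38/0.263 = 1.45 standard errors. For n = 35 it is √(2/35) = 0.239, and 0.38/0.239 = 1.59. Simulated power is 0.27 to 0.28 at N = 58 and 0.32 to 0.33 at N = 70. For a slope difference of 0.6 it is 0.58 and 0.66.

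**2. Fidelity: what any two-arm model can do with it**

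Inputs: log kept in the COS-P arm only; groups of 8 to 10 carers. With 35 carers, 35/10 = 3.5 and 35/8 = 4.4, so about four COS-P groups and about four distinct fidelity values.

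- *Controls left missing.* A complete-case fit drops the whole control arm, and group becomes a constant (rank 1 for the two columns intercept and group). If PBA and SAQ are in the same model, their comparison between arms is lost too.
- *Controls coded 0 on the raw scale.* With illustrative group means of 4.0, 4.2, 4.4 and 4.6, the correlation of fidelity with group is 0.997, and the variance inflation factor is 1/(1 - r²), about 190. Adding a product does not help: group × fidelity equals fidelity (rank 3 for four columns).
- *Fidelity centred on the COS-P mean, controls set to 0.* The correlation with group is 0 and the design has full rank (3 of 3). The fidelity coefficient is then the slope within the intervention arm, which is not a between-arm moderation effect.

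**The case against.** The strongest reply is that the article condenses a fuller plan. It says that the moderators enter after group, not that they enter only as main effects. Hierarchical regression is a common vehicle for an interaction step, and the stated purpose is moderation. An analysis plan that is not shown could add the products for PBA and SAQ. This limits the claim to the model as described. It does not remove it, because the article gives the outcomes, the predictors and the order of entry, and the model so described is additive. No such addition could make fidelity a between-arm moderator.

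Several stronger readings are tempting, and the article does not support them:

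- *A reader might infer that the group effect cannot be estimated once fidelity enters.* Group is entered first, so its effect is estimated before that. It also stays estimable if fidelity is centred within the COS-P arm. The article specifies neither complete-case deletion nor raw zero coding.
- *A reader might infer that post-treatment PBA and SAQ values will be used.* The article names no time point. What stands is that it should, since a T2 value may itself be affected by COS-P.
- *A reader might infer that the planned model will always miss true moderation.* The contrast of 7% with 86% needs slopes that cross and average to zero. With slopes of 0 and 0.4 both terms reject in about 31% of trials.
- *A reader might infer that the whole objective is lost.* Burnout and support are also covered by focus groups and self-confrontation interviews (Table 4).

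The objection on weight stands as well. The analysis is labelled exploratory throughout, and H1 and H2 are tested by separate mixed ANOVAs that contain no moderator.

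**Conclusion.** The concern holds for the model as described. For PBA and SAQ, the second step tests prognosis and not moderation. With a purely prognostic moderator at r = 0.4 and 28 carers per arm, it would be significant in about 88% of trials, against about 5% for the term that does test moderation. The exact percentages rest on the assumed slopes; the structural conclusion does not. The 88% is not an error rate for the regression itself. It becomes one only if the coefficient is reported as moderation, which is the stated purpose. For fidelity, the conclusion follows from Table 3 and needs no simulation: a variable recorded in one arm, with about four distinct values, cannot be a between-arm moderator.

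Severity is moderate. No confirmatory estimate, test or sample size changes.

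**What to change.** Reword the moderation paragraph as follows:

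- Add group × PBA and group × SAQ terms, with the main effects kept in the model.
- State that the T1 values of PBA and SAQ are used.
- Judge moderation only on the product terms, reported with 95% confidence intervals. Report the moderators' main effects as prognostic associations.
- Take fidelity out of the two-arm regressions and describe it by COS-P group within the intervention arm.

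Adjusting for the T1 outcome and fitting one model per moderator are sensible options, but they do not correct an error.

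The cost is a few sentences and a few lines of R. All the data are already scheduled, so no visit, measure or participant is added. The drawback is low power: about 0.3 for a slope difference of about 0.4. A non-significant product term must not be read as absence of moderation, and the findings remain exploratory.

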**Fig. 3 Fig3:**
[figure not shown]
CONSORT diagram describing flow of participants through study

## Discussion

This study protocol outlines a mixed-methods randomized controlled trial designed to evaluate the effectiveness of the Circle of Security Parenting program^®^ (COS-P) for foster carers in France. The study aims to demonstrate the program’s impact on several key outcomes. Primarily, it seeks to assess whether COS-P can improve foster carers’ caregiving sensitivity, particularly their parental reflective functioning. Secondly, it will examine if COS-P enhances the quality of the relationship between foster carers and foster children. Additionally, the study will explore potential moderating factors, such as foster carer burnout and perceived support from child protective services (CPS), and delve into participants’ subjective experiences with the program.

This study addresses a critical gap in the literature by conducting the first evaluation of COS-P specifically for foster carers in France. While previous research has established the efficacy of COS-P in improving parenting outcomes in other populations, including mothers and residential care workers, this study will provide valuable insights into the program’s applicability and effectiveness within the unique context of the French child protection system.

The study boasts several strengths, including its randomized controlled trial design. Furthermore, the use of validated and reliable measures strengthens the study’s methodological rigor. By incorporating both quantitative and in-depth qualitative data, the study aims to provide a comprehensive and nuanced understanding of the program’s impact.

However, the study also acknowledges certain limitations. Firstly, its geographic scope is limited to one region in France, which may constrain the generalizability of the findings. Secondly, the relatively short follow-up period may not fully capture the long-term impact of the intervention. Finally, a potential for selection bias exists. Foster carers who choose to participate in the study might already be more engaged in their relationships with foster children and more emotionally supportive compared to those who decline participation. This pre-existing difference could lead to an underestimation of the program’s effects on caregiving sensitivity.

Despite these limitations, findings from this study hold significant implications for policy and practice within the French child protection system. Should COS-P prove effective, it could be integrated into pre-service or continuing education programs for foster carers. Such integration has the potential to enhance the quality of care provided to children in out-of-home placements, ultimately contributing to improved outcomes for this vulnerable population. Furthermore, the study’s findings could inform the development of tailored interventions that address the specific needs of foster carers, including interventions that target burnout and bolster support networks. Looking ahead, future research should prioritize exploring the long-term impact of COS-P and delve into its effectiveness across different cultural contexts.

